
*Statistical analysis*

Sample size. The sample size of the present study was calculated with Sampsize.31 Assuming a power of 80% and an alpha error of 2.5%, for a standardised non-inferiority margin equivalent to 0.25, a sample size of 366 subjects (183 for each arm) will be needed to demonstrate non-inferiority of the intervention by remote versus standardised means, relative to the primary outcome (self-care maintenance). Estimating a possible dropout of 10% at 1 month after the end of the educational intervention, it will be necessary to enrol 384 subjects (192 for each arm). Considering that there will be six centres participating in the study, each centre will enrol 64 patients (32 per arm).

Non-inferiority margins. The non-inferiority margin established for the primary outcome (self-care maintenance) will be four points. This margin corresponds to half of the minimum score considered clinically significant (equivalent to 0.5 standard deviations) on the standardized scales of self-care^32^. The choice of this margin of inferiority arose after careful clinical judgment of the research team and based on the general recommendation to adopt a value that is smaller than the minimum clinically significant score and is, at the same time, clinically irrelevant ^33^.

For secondary outcomes self-care monitoring, self-care management and self-efficacy, the same margin of non-inferiority is established, a difference of 8 points being valid in these scales as the minimum clinically significant score ^32^.

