Planned statistical analyses. Sociodemographic and clinical characteristics, as well as outcome scores, will be described by measures of central tendency (mean or median) and variability (standard deviation or interquartile range), while frequencies and percentages will be used for categorical variables. To investigate differences in sociodemographic and clinical characteristics between randomisation groups, the t test for independent samples and the chi-square test will be used. P values less than 0.05 will be considered statistically significant. To investigate differences in the primary outcome and secondary outcomes of non-inferiority, the student's t test for independent samples will be employed at each follow-up and baseline. A longitudinal linear mixed model will be implemented to analyze the effect of interventions on randomization groups and their interaction with time. This approach, widely used as a substitute for ANOVA (in order to avoid loss of subjects due to missing data), has the advantage of controlling for the phenomenon of "clustering" induced by repeated measures over time for each subject.^34^

Non-inferiority of the experimental intervention remotely compared with the in-presence intervention will be confirmed if the lower extreme of the 95% confidence interval is not below the predetermined non-inferiority margin. Any superiority of the experimental intervention over the active control will be confirmed if the lower end of the 95% confidence interval is simultaneously above the non-inferiority margin and above zero. Given the nature of non-inferiority trials, analyses will be conducted in both intention-to-treat and per-protocol modes, according to CONSORT recommendations.^33^ The hypothesis of non-inferiority will be confirmed only if obtained through both modes of analysis.^35^ For missing data analyses, the distributions of patients lost to follow-up between the two randomisation groups will be compared (using chi-square tests) in order to assess any differences in sociodemographic and/or clinical characteristics, or outcomes. The results obtained will be interpreted in light of any differences found between the groups.

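### The protocol's missing-data procedure changes no estimate, and the test named for non-inferiority uses observed scores only, so the intention-to-treat result at 1 month is in effect a completers' analysis

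*Protocol*

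**What the plan says.** All of this is in the Protocol, METHODS, Statistical analysis.

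- **Missing data.** Under Planned statistical analyses, "the distributions of patients lost to follow-up between the two randomisation groups will be compared (using chi-square tests") to look for differences in sociodemographic or clinical characteristics, or outcomes. The consequence is stated as: "The results obtained will be interpreted in light of any differences found between the groups".
- **Test for the non-inferiority outcomes.** For the primary and secondary outcomes, "the student's t test for independent samples will be employed at each follow-up and baseline".
- **Mixed model.** "A longitudinal linear mixed model will be implemented to analyze the effect of interventions on randomization groups and their interaction with time". One reason given for it is "in order to avoid loss of subjects due to missing data".
- **Decision rule.** Non-inferiority "will be confirmed if the lower extreme of the 95% confidence interval is not below the predetermined non-inferiority margin". The rule does not say whether the interval comes from the t test or the mixed model.
- **Analysis sets.** Intention-to-treat and per-protocol are both used: "The hypothesis of non-inferiority will be confirmed only if obtained through both modes of analysis".
- **Expected loss.** Under Sample size: "Estimating a possible dropout of 10% at 1 month after the end of the educational intervention", with 192 patients enrolled per arm.

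The primary endpoint is self-care maintenance 1 month after the educational intervention ends. In Table 2 this is the first assessment after baseline.

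**The concern.** The one procedure introduced as the missing-data analysis does not act on the result. If the chi-square comparison is not significant, it is likely to be read as reassurance. If it is significant, the estimate, interval and decision are still the same.

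The direction of bias matters more than usual in a non-inferiority trial. If patients who gain little from video sessions leave before month 1, the observed remote-arm mean rises and the comparison moves towards success. Equal loss rates do not exclude this. Remote patients may leave because the sessions do not help them, and in-person patients because they tire of travelling. The loss counts would then match although the missing scores differ.

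Much rests on the claim. The Conclusions section says that confirmation would make remote education the treatment of choice.

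**Working it through.** **Inputs from the protocol**
- Margin: 4 points, stated as half of the minimum clinically significant score, which is put at 0.5 SD. The minimum is therefore 8 points and the SD is 8 / 0.5 = 16.
- Enrolled: 192 per arm. Planned loss: 10% at 1 month. Lost: 0.10 × 192 ≈ 19 per arm. Analysed: 192 - 19 = 173 per arm.
- Alpha: 2.5%, taken as one-sided, matching the lower limit of a 95% interval.

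**The plan's own loss allowance.** 366 / 0.90 ≈ 407, not the stated 384. An enrolment of 384 allows for 1 - 366/384 = 4.7% loss. That mismatch is a separate matter. The figures below use the stated 192 per arm and 10% loss.

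**Assumption not in the protocol.** Remote-arm dropouts would have scored *g* points below remote completers at month 1, and there is no such gap in controls. The values *g* = 4, 8 and 16 show the range.

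**Step 1: bias of the completers' comparison**

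Difference among completers = true difference + 0.10 × *g*. With a true difference of -4, at the margin, this is -3.6, -3.2 and -2.4 for the three gaps.

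**Step 2: false non-inferiority with the t test (normal approximation)**

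SE = 16 × √(2/173) = 1.72.

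P(false non-inferiority) = P(Z > 1.96 - 0.10 × *g* / 1.72)

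| Gap *g* (points) | Bias (points) | Threshold for Z | False non-inferiority |
|---|---|---|---|
| 0 | 0 | 1.96 | 2.5% |
| 4 | 0.4 | 1.73 | 4.2% |
| 8 | 0.8 | 1.49 | 6.7% |
| 16 | 1.6 | 1.03 | 15.2% |

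**Step 3: what the chi-square check can show (two-sided 5%)**
- Loss of 7% v 13%, 192 per arm: power about 50%.
- Equal loss in truth: the comparison of loss rates flags a difference no more often than its 5% error rate, whatever the missing scores are.
- A characteristic present in 30% v 60% of those lost, 19 per arm: power about 46%.
- Loss of 15% v 5%: p = 0.001, so grossly unequal loss would be noticed, but nothing would be corrected.

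**Step 4: does the mixed model help?** A simulation used 4,000 trials per scenario, 192 per arm, 10% lost in each arm, SD 16 and a true difference of -4. It assumed a baseline-to-outcome correlation of 0.5, which the protocol does not give. A baseline-adjusted model stood in for the mixed model at month 1.

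| Dropout pattern | t test: bias; false non-inferiority | Baseline-adjusted: bias; false non-inferiority |
|---|---|---|
| Random | 0.02; 2.6% | 0.02; 2.7% |
| Remote dropouts about 16 points below completers | 1.56; 14.7% | 1.20; 11.9% |

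The simulated 14.7% agrees with the 15.2% in Step 2. Adjustment removed (1.56 - 1.20) / 1.56 = 23% of the bias, because a patient lost before month 1 has only a baseline score to contribute.

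**Step 5: does requiring both analysis sets help?** With the t test, a patient without a 1-month score is absent from the intention-to-treat comparison and from the per-protocol comparison. Agreement between the two gives no protection against this loss.

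**The case against.** **This is SAP material.** Imputation models and tipping-point analyses are usually left to the SAP, and no SAP is shown. That is right for their details, and their absence alone would be no finding. But the protocol itself fixes a procedure for missing data and names the test for non-inferiority. The objection is to those two choices.

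**The mixed model is a second missing-data measure.** This stands. A reader might infer that the chi-square comparison is the whole plan and that nothing protects the claim. The text does not support that: the mixed model is there partly to keep patients with incomplete data, and it is valid when missingness depends only on observed data. What remains is that it is not linked to the non-inferiority decision and has little to work with for early losses.

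**Outcomes of those lost can be compared in part.** This also stands. Baseline scores exist for everyone, and patients lost after month 1 have a month-1 score. Only the scores that decide the primary endpoint are out of reach.

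**No analysis can detect dropout that depends on unseen scores.** True, and multiple imputation under the usual assumption shares this limit with the mixed model. Only a sensitivity analysis can show how much the conclusion depends on it.

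**The effect is modest and assumed to run one way.** Largely true. An 8-point gap moves the estimate by 0.8 points. Hiding the whole 4-point margin at 10% loss would need a gap of 4 / 0.10 = 40 points. Patients must be able to make video calls and be free of stomal complications at entry, which may limit selective loss from the remote arm.

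**Conclusion.** The point holds in a limited form. The stated check on losses changes no estimate, is weak at about 19 lost per arm, and cannot reach the scores that matter. As worded, the non-inferiority test is a completers' analysis in both analysis sets.

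False non-inferiority would be about 4%, 7% or 15% instead of 2.5% for gaps of 4, 8 or 16 points. This rests on SD 16, 10% loss per arm, a true difference exactly at the margin, a t test, and a gap in the remote arm only. The last is an assumption with no support in the protocol either way; poor performers leaving the control arm would bias against non-inferiority.

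A reader might go further and infer that remote-arm failures will leave and that a clearly inferior intervention could pass. The document does not show this. In the simulation with a gap of about 16 points and a true difference of -6, the t test confirmed non-inferiority in only 1.4% of trials. The exposure lies mainly near the margin. The plan should be changed, but this does not invalidate the trial.

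**What to change.** In Planned statistical analyses, replace the missing-data sentences and state the following.

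1. The intention-to-treat non-inferiority interval at 1 month is based on all randomised patients. It comes from the already planned mixed model with the baseline score as part of the model, or from multiple imputation using baseline, stratification factors and available follow-up scores.
2. A prespecified tipping-point sensitivity analysis lowers the imputed remote-arm scores in steps, for example 0, 4, 8, 12 and 16 points, and reports the shift at which non-inferiority is lost. The protocol's own 8-point clinically significant difference serves as a reference for judging that shift, not as a pass/fail rule.
3. Counts, reasons and characteristics of patients lost are described by arm, without significance tests.

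The cost is a paragraph of wording and a few more analysis runs, with no new patients or visits. The small downside is that a borderline result may have to be reported as sensitive to missing data.

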**CONCLUSIONS**

The prevalence of ostomy patients is likely to increase in the future due to an aging population and an increase in the prevalence of chronic diseases. Self-care education delivered remotely has the potential to be on par (or superior) in effectiveness with traditional education delivered in person, possibly resulting in improved health outcomes. If this hypothesis were to be confirmed, it would be appropriate to make remote education the treatment of choice to meet the educational needs of ostomy patients in the postoperative period, and as a response to the changes originating from the COVID-19 pandemic.

| Variables | Tool | Time of Data Collection  (after educational intervention) | | | |
| --- | --- | --- | --- | --- | --- |
|  |  | **Baseline** | **1 month** | **3 months** | **6 months** |
| Cognitive Status | Six-item Screener | x |  |  |  |
| Sociodemographic and clinical characteristics | Ad hoc questionnaire | x |  |  |  |
| Comorbidities | CCI | x |  |  |  |
| Self-care maintenance, monitoring, management and self-efficacy | OSCI | x | x | x | x |
| Quality of life | Ostomy QoL | x | x | x | x |
| Depression | PHQ-9 | x | x | x | x |
| Adaptation, coping | OAI-23 | x | x | x | x |
| Stomal and peristomal complications | Ad hoc questionnaire | x | x | x | x |
| Number of improper accesses to health services | Ad hoc questionnaire | x | x | x | x |
| Lost working days | Ad hoc questionnaire | x | x | x | x |
| Mobility | Ad hoc questionnaire | x | x | x | x |

**Legend.** CCI, Charlson's Comorbidity Index; OAI-23, Ostomy Adjustment inventory-23; OSCI, Ostomy Self-care Index; QoL, Quality of Life.

